### Sample size

Values of cancer-related distress on the Impact of Event Scale (IES–Total) range from 0 to 75. Based on prior intervention studies of breast cancer patients and their partners using IES–Total (Scott et al. 2004; Manne et al. 2005b), we estimated the mean of the patients to be 27 at baseline with a standard deviation (SD) of 16.5. Congruous to these previous studies, we considered a difference of 7 points clinically relevant. With a power of 0.90 and an alpha of 0.05, we aimed to include 220 couples.

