### Randomisation

Randomisation was conducted following return of the signed informed consents and baseline questionnaires from patient and partner. Couples were randomised to the intervention or control group according to a computer-based randomisation procedure. The randomisation program was developed by a statistician of the research group and administered by an independent research assistant. The randomisation procedure was stratified on centres and each centre was block randomised in sequences calculated on the basis of each centre’s annual number of breast cancer surgeries. The block randomisation should ensure a more constant workload for the psychologists who had permanent positions in parallel with the project. All except the statistician were blinded to the block sizes and allocation sequence.

Couples were phoned by the project manager and informed about randomisation allocation. Obviously participants were not blinded with regard to the group assignment. Due to geographical reasons it was not possible to randomise the psychologists to centres.

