Furthermore, the HiH intervention addressed both distressed and non-distressed breast cancer patients and partners. We planned an intervention addressing attachment security and promoting new emotional experiences in a safe environment. A limitation of our design is that we compared the HiH intervention in addition to usual care with usual care only. It may be difficult to interpret the results with regard to the effect of the intervention, because a possible effect may be due to the mere fact that the intervention makes it possible for the couple to benefit from having leisure time together in a stressful situation.

To enhance protocol adherence, we made a treatment fidelity checklist to measure if the session had been performed in compliance with the intervention guide.

Some patients and/or partners declined to participate, because they felt overwhelmed by their new life situation and ongoing treatment or did not have the time to participate. Therefore, our sample might not be representative of primary breast cancer patients and their partners in general. We will address this by comparing characteristics of participants and non-participants.

By December 2013, the HiH study had succeeded in including 199 couples. Our sample size of 220 couples was calculated with a 0.90 power. Due to the fact that the inclusion at Centre 3 was delayed, we redid the sample size calculation with a 0.80 power. Based on this calculation, we wanted to include 166 couples. To take into account a risk of attrition of 20% we included 199 couples.

To conclude, receiving attachment-oriented psychological counselling in the early treatment phase is expected to reduce distress and to improve dyadic adjustment and health-related quality of life in breast cancer patients and their partners. If proven effective, this intervention would be helpful in optimising psychosocial care and rehabilitation of couples coping with breast cancer.

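### The 220-couple target is stated at 0.90 power without an attrition allowance; on the stated inputs it gives about 0.88 with no loss and about 0.80 at the 20% loss assumed elsewhere

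*Protocol article*

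**What the plan says.** The Sample size section of the protocol article sets out the inputs on IES-Total. It expects a baseline mean of 27 "with a standard deviation (SD) of 16.5", and "we considered a difference of 7 points clinically relevant". It then concludes: "With a power of 0.90 and an alpha of 0.05, we aimed to include 220 couples". That section does not mention loss to follow-up.

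The Discussion returns to the subject. It says "Our sample size of 220 couples was calculated with a 0.90 power", and that the calculation was redone at 0.80 power, giving 166 couples, because inclusion at Centre 3 was delayed. Only then does attrition appear: "To take into account a risk of attrition of 20% we included 199 couples".

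The Statistical methods section plans a linear regression adjusted for baseline for the primary outcome. No baseline-to-follow-up correlation is given there or in the sample size text.

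**The concern.** Under Recruitment, inclusion required consent and completed baseline questionnaires, so couples are included before any follow-up. A target for included couples therefore delivers its stated power only if it allows for couples who have no 5-month value. The Discussion makes that allowance for the 0.80-power target. Nothing shows that it was made for the 0.90-power target, and the figures indicate that it was not.

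The Methods section thus attaches 0.90 to an enrolment number that would not give 0.90 under the article's own attrition assumption. A reader who takes the power from Methods would overrate the planned sensitivity to a 7-point difference, which matters most when interpreting a null result.

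**Working it through.** **Inputs.** From the Sample size section: difference 7, SD 16.5, alpha 0.05, power 0.90, N = 220. From the Discussion: power 0.80, N = 166, attrition 20%, 199 included. The article does not state sidedness, allocation ratio or whether the sizing used baseline adjustment. I assume two-sided, 1:1 and an unadjusted comparison of two means.

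**Step 1: reproduce 220.** By the normal approximation, total N = 4(z₁ + z₂)² × SD² / 7².
- SD 16.5, power 0.90: 4 × (1.960 + 1.282)² × 16.5² / 49 ≈ 233.5, or 234 couples (117 per arm). The t-based answer is 235.5, or 236 in equal arms.
- SD 16.5, power 0.80: 88 per arm, 176 couples, against the stated 166.

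Both published figures are about 6% below what the stated SD requires. An SD of 16.0, which the article does not give, comes close to both: 219.6 for 0.90 (normal approximation) and 166.0 for 0.80 (t-based).

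**Step 2: does 220 include attrition?**
- 220/166 = 1.325. The theoretical ratio for 0.90 against 0.80 power is (1.960 + 1.282)² / (1.960 + 0.842)² = 1.339. The two figures therefore share a basis.
- The Discussion adds attrition after 166 (166 × 1.2 = 199.2), so 166 is before attrition, and by the shared basis so is 220.
- At SD 16.5, 0.90 power already needs 234 to 236 couples with no loss, so an unadjusted two-sided 220 leaves no room for an allowance.
- A one-sided test does not explain it either. It needs 192 for 0.90, which inflates to 192 × 1.2 ≈ 231 or 192/0.8 = 240, not 220.

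**Step 3: power by evaluable number** (noncentral t, two-sided 0.05, N/2 per arm).

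| Couples included | Loss | Evaluable | SD 16.5 | SD 16.0 |
|---|---|---|---|---|
| 220 | 0% | 220 | 0.879 | 0.898 |
| 220 | 10% | 198 | 0.844 | 0.865 |
| 220 | 20% | 220 × 0.80 = 176 | 0.799 | 0.823 |
| 199 | 20% | 199 × 0.80 ≈ 159 | 0.758 | 0.783 |

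If 20% is read as dividing by 1.2, then 220/1.2 ≈ 183 are evaluable, and power is 0.814 (SD 16.5) or 0.837 (SD 16.0).

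**Step 4: sensitivity to baseline adjustment.** The residual SD is 16.5 × √(1 − r²), where r is an assumed correlation. Power at 176 evaluable is 0.835 for r = 0.3, 0.863 for r = 0.4, 0.898 for r = 0.5 and 0.938 for r = 0.6.

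**The case against.** **The target was superseded.** The Discussion says that the calculation was redone at 0.80 and an attrition allowance added. The operative number is therefore 199, and nobody need read the results against 0.90. This stands and limits the point to reporting. It does not remove it, because 220 at 0.90 is still the only target in the Sample size section.

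**The 20% is carried backwards.** It appears once, for the revised target. That is true, but no lower rate is given for 220. At 10% loss power is still 0.84 to 0.87, and at SD 16.5 it is 0.88 with no loss at all.

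**Baseline adjustment could restore 0.90.** At an assumed r of 0.5, about 176 evaluable couples give 0.90, and 176/0.80 is exactly 220. The ratio in step 2 cannot exclude this by itself, since it shows only that 220 and 166 share a basis. What counts against it is that the Discussion adds attrition after 166, and that the article neither states a correlation nor claims such a gain. The possibility does rule out one tempting inference, that the plan was never powered at 0.90. The documents do not support a statement that strong.

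**The redesign is described fairly.** A reader might also infer that the Discussion misrepresents the change by presenting 220 down to 199 as 0.90 down to 0.80. It does not. It ties the change in power to 220 against 166, both before attrition, and reaches 199 in a separate step.

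**Conclusion.** The point holds as a minor reporting error. The 220-couple target carries no visible attrition allowance and does not give 0.90 power on the stated inputs: about 0.88 with no loss and about 0.80 with 20% loss. With an SD of 16.0 the figures are 0.90 and 0.82. At 20% loss the shortfall from 0.90 is thus 8 to 10 percentage points. On the same footing, the 199 couples included leave about 159 evaluable and give 0.76 to 0.78.

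All these figures assume a two-sided 0.05 test, 1:1 allocation and no baseline adjustment. Adjustment would raise them by an amount that the article does not let a reader calculate.

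**What to change.** In the Sample size section, state that 220 makes no allowance for attrition, and restate its power as about 0.88 with no loss and about 0.80 at 20% loss. Alternatively, give the SD or baseline correlation actually used, with the matching figures. Simply relabelling 220 as the evaluable number for 0.90 would not do, because the stated SD of 16.5 does not reproduce it.

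In the Discussion, add that 199 included couples leave about 159 evaluable at 20% loss, with power of about 0.76 at SD 16.5 (0.78 at SD 16.0) before any gain from baseline adjustment. The comparison of 220 with 166 can stay as it is.

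The cost is a few sentences and a less favourable stated power. No couples, data or analyses change.

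### The stated sample sizes (220 couples for 0.90 power, 166 for 0.80) do not follow from the stated SD of 16.5 and 7-point difference

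*Protocol article*

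**What the plan says.** All figures are in the protocol article.

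- **Sample size section.** From earlier intervention studies, "we estimated the mean of the patients to be 27 at baseline with a standard deviation (SD) of 16.5". On the effect to detect: "we considered a difference of 7 points clinically relevant". The target follows directly: "With a power of 0.90 and an alpha of 0.05, we aimed to include 220 couples".
- **Discussion.** Because one centre started late, "we redid the sample size calculation with a 0.80 power". The result: "Based on this calculation, we wanted to include 166 couples". Then: "To take into account a risk of attrition of 20% we included 199 couples".
- **Statistical methods section.** The primary outcome, change in patients' IES from T1 to T2, is analysed by linear regression with adjustment for baseline.

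The article does not say whether alpha is one- or two-sided, what the allocation ratio is, or what correlation between baseline and T2 was assumed. It gives no SD other than 16.5.

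**The concern.** The article prints every input of a standard two-group calculation (SD, difference, alpha, power) together with its result, twice. A reader can therefore check it, and both results come out about 6% below what the inputs require. The same gap at both powers suggests a wrong or unreported input rather than rounding.

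The numbers matter because readers will use the quoted powers to judge how informative a null result is. The 0.80 calculation also carries the decision to lower the target from 220 to 166 and then to enrol 199.

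**Working it through.** **Inputs from the article.** SD 16.5, difference 7, alpha 0.05 and power 0.90 (Sample size section); power 0.80 (Discussion).

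**Assumptions, not stated there.** Two-sided alpha, 1:1 allocation, unadjusted comparison of means. Alternatives are tried in step 4.

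**Formula.** n per arm = 2 × (z₀.₉₇₅ + z_power)² × SD² / 7², with z = 1.960, 1.282 (0.90) and 0.842 (0.80). The squared sums are 10.507 and 7.849.

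**1. Trying to reproduce the plan's figures with SD 16.5** (SD² = 272.25)

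- 0.90: 2 × 10.507 × 272.25 / 49 = 116.8, so 117 per arm, **234 couples** (stated 220, short by 14, or 6.0%).
- 0.80: 2 × 7.849 × 272.25 / 49 = 87.2, so 88 per arm, **176 couples** (stated 166, short by 10, or 5.7%).
- With the t distribution: 117.7 and 88.2, so 118 and 89 per arm, 236 and 178 couples. The gap widens slightly.

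**2. Power at the stated numbers with SD 16.5**

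| Couples | Claimed | Normal approximation | t distribution |
|---|---|---|---|
| 220 | 0.90 | 0.882 | 0.880 |
| 166 | 0.80 | 0.780 | 0.776 |

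The difference detectable with 166 couples at 0.80 power is 16.5 × √(2/83) × (1.960 + 0.842) = 7.2 points instead of 7.

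**3. What does reproduce them: SD 16.0** (SD² = 256), same normal formula

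- 0.90: 2 × 10.507 × 256 / 49 = 109.8, so 110 per arm, **220 couples**.
- 0.80: 2 × 7.849 × 256 / 49 = 82.01, so 83 per arm, **166 couples**.

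Solving backwards, 220 requires an SD between 15.94 and 16.02, and 166 requires one between 16.00 and 16.10. The overlap is about 16.00 to 16.015.

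**4. Other readings of the stated inputs** (SD 16.5)

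| Reading | 0.90 | 0.80 |
|---|---|---|
| Stated in the article | 220 | 166 |
| One-sided alpha 0.05 | 192 | 138 |
| Allocation 1.5:1 | 245 | about 183 |
| Allocation 2:1 | 264 | 198 |
| Change score without baseline adjustment, r = 0.5 | 234 | 176 |
| Baseline-adjusted, r = 0.2 | 226 | 168 |
| Baseline-adjusted, r = 0.3 | 214 | 160 |

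The adjusted rows use SD × √(1 − r²), where r is an assumed baseline-to-T2 correlation. An adjusted SD of 16.0 corresponds to r = √(1 − (16/16.5)²) = 0.244, so r of about 0.24 with SD 16.5 also yields both stated numbers.

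Also, 176 / (1 − 0.20) = 220. But the article ties 220 to 0.90 power and names no attrition allowance for it, and this route leaves 166 unexplained.

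**5. The trial as enrolled** (SD 16.5, unadjusted)

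- 199 couples, no loss: power 0.85.
- 199 × 0.80 = about 159 couples: power 0.76.

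**6. The planned baseline-adjusted analysis** (r assumed)

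| Couples | r = 0.25 | r = 0.50 |
|---|---|---|
| 220 | 0.90 | 0.95 |
| 166 | about 0.80 | 0.88 |

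With 159 couples, r = 0.30 brings power back to about 0.80.

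**The case against.** The strongest reply is that 16.5 is described as the SD at baseline, whereas the primary test is a regression adjusted for baseline. The SD that governs that test is the residual SD, which the article does not print. A modest correlation of about 0.25 restores both quoted powers, and a correlation of 0.50 exceeds them. A condensed article may also leave the correlation to the full protocol or analysis plan, so its absence is not itself a fault.

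Much of this stands. A reader might infer from the mismatch that the claimed powers are too high for the trial's actual analysis. The documents do not support that: the shortfall is shown only for an unadjusted comparison. A reader might also infer that the trial lacks its claimed power even before attrition. That is wrong for the trial as enrolled, because 199 couples give about 0.85 unadjusted, above the claimed 0.80.

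The reply does not make the printed figures agree. The Sample size section presents a baseline mean, an SD, a difference, alpha, power and a total, with nothing to show that baseline adjustment was credited. A correlation that is not stated cannot be assumed to have been part of the calculation.

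**Conclusion.** The point holds as an error in stated figures. With SD 16.5, a 7-point difference and two-sided alpha 0.05 in equal arms, 234 and 176 couples are needed, not 220 and 166. The stated numbers correspond to unadjusted powers of about 0.88 and 0.78. This rests on the two-sided, 1:1 reading; the one-sided and unequal-allocation alternatives tried do not reproduce the numbers either.

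The likeliest cause is that SD 16.0 was used and 16.5 printed. A reader might take the exact match as proof, but it remains an inference, because SD 16.5 with a correlation of about 0.24 fits equally well.

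The consequence is small: about two percentage points of power, and 7.2 instead of 7 points detectable. Unadjusted power does fall to about 0.76 if the full 20% is lost, but the planned adjustment could recover that at a correlation of about 0.30. The trial is not shown to be materially underpowered. This is a minor but real inconsistency.

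**What to change.** Make the Sample size section and the Discussion agree with their inputs, in one of two ways:

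1. Report the SD actually used, or the correlation if one was used, and justify it from the cited studies.
2. Keep SD 16.5 and restate the unadjusted powers as about 0.88 for 220 couples and 0.78 for 166. Add the power of the planned baseline-adjusted regression under an explicit assumed correlation: for 166 couples, about 0.80 at r = 0.25 and 0.88 at r = 0.50.

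Either way, state that alpha is two-sided and allocation equal, if that is so, so that the calculation can be repeated. The cost is a corrected sentence in each of the two sections and, under the second option, slightly less favourable unadjusted powers. Enrolment, design and analysis stay as they are.

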### Statistical methods

The primary outcome being change in breast cancer patients’ cancer-related distress between T1 and T2 will be analysed with a linear regression, adjusted for baseline. Secondary outcomes will be analysed by means of multilevel analysis. Secondary analysis will be performed for selected variables and the effect over time on distress will be analysed. Factors that can affect level of distress will be investigated and adjusted for. Data on patients and partners as individuals will be analysed with multilevel techniques. Modified ITT analysis will be performed with a clear description of exactly who was included in each analysis.

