### Recruitment

Participants were recruited at three Danish breast surgery departments: Ringsted Hospital (Centre 1), Odense University Hospital (Centre 2) from October 2011 to December 2012 and Herlev University Hospital (Centre 3) from April 2012 to January 2013. All centres treated patients from both rural and urban areas. Eligible patients received oral and written project information from a nurse or a healthcare worker during the medical discharge consultation after surgery or at the first following outpatient consultation. Patients were asked for permission to be phoned by the project manager within few weeks after the first outpatient consultation.

During phone contact, patients received a summary of the study and were given the opportunity to raise questions or concerns related to the study. Partners of patients who were interested in participation were then contacted and provided the same project information. Inclusion required written consent to participate and completed baseline questionnaire from both the patient and the partner.

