### Usual care

Both the intervention and control group received usual care at the centres. Usual care involved oral and written information about frequent psychological reactions to receiving a cancer diagnosis. Two centres had additional offers. At *Centre 1* patients could be referred to psychological counselling with the in-house psychologist, i.e. a project psychologist. Emotionally distressed families with younger children could receive counselling by the in-house psychologist and a social worker from the Danish Cancer Society. *Centre 3* offered all breast cancer patients a free daytime seminar lasting three and a half day. Seminar participants received information about medical, psychological and social aspects of breast cancer.

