#### Potential covariates

Clinical and demographic data included age, length of intimate relationship, education, stage of disease and treatment received for patients. These data were obtained from clinical databases, except length of intimate relationship, which was self-reported. The therapeutic alliance between participants in the intervention group and the psychologists was assessed by participants using the subscale “Bond” in the Working Alliance Inventory (WAI-SR) (Hatcher & Gillaspy 2006). Attachment style and dimensions of avoidance and anxiety were assessed by the Relationship Questionnaire (RQ)(Bartholomew & Horowitz 1991).

All outcomes were assessed at T1, T2 and T3; except post-traumatic growth, intimacy and involvement of the partner, which were not included at T1 and the “Bond” subscale of the WAI, which was only measured at T2. Couples, who had been in contact with the project manager but declined to participate, were asked to fill in a baseline questionnaire. The data will be used for a comparison of participants and non-participants.

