## Discussion

To our knowledge HiH is the first psychological attachment-oriented couple intervention, targeting both initially distressed and non-distressed breast cancer patients and partners, that has been tested in a randomised controlled trial setting. Moreover, the focus on interdependent coping in the early treatment phase is a unique aspect. Conversely to other psychological interventions for patients and partners facing breast cancer, the HiH intervention used a semi-structured protocol, allowing adjustment of the intervention with regard to the number and content of the sessions.

We developed an intervention for couples who are distressed in the early breast cancer trajectory and non-distressed couples who may become distressed during the breast cancer trajectory. The aim was to reduce distress. The number of 4 to 8 sessions was estimated to be adequate to help couples to gain attachment security and to create new emotional experiences, thereby reducing and preventing distress.

Furthermore, we know that usual care varies across centres. However, we took great care to ask all participants at T3 if they had received any additional support and counselling (other than the intervention), and by whom this support has been provided. This information will be helpful in the interpretation of the results.

We have included therapeutic alliance and attachment-related anxiety and avoidance as potential covariates. Thereby we can ascertain potential moderating effects in the relationship between the participants and the psychologists. The measure of attachment-related anxiety and avoidance can help us to understand, if for example patients high on attachment-related anxiety benefit more from the intervention compared to patients low on attachment-related anxiety.

Results from previous intervention studies of breast cancer patients and their partners have been substantially influenced by methodological limitations such as small sample sizes, large attrition rates, inadequate description of attrition rates, and lack of specific randomisation procedures (Regan et al. 2012; Badr & Krebs 2013). We took the challenge to design and conduct a multi-centre, randomised, controlled trial that overcomes these limitations.

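### The primary regression names baseline IES but not centre, the factor randomisation was stratified by; naming centre would be a small, nearly free gain in precision

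*Protocol article*

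**What the plan says.** All references are to the protocol article.

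- **Recruitment:** "Participants were recruited at three Danish breast surgery departments". Centre 3 started later than the other two.
- **Randomisation:** "The randomisation procedure was stratified on centres and each centre was block randomised in sequences". The same section says the psychologists could not be randomised to centres.
- **Usual care:** a common package of information, and then "Two centres had additional offers". Centre 1 could refer patients to an in-house psychologist, and Centre 3 offered all patients a seminar.
- **Discussion:** "we know that usual care varies across centres". The stated response is to ask at T3 about other support received and to use the answers when interpreting results.
- **Statistical methods:** the primary outcome "will be analysed with a linear regression, adjusted for baseline". After the secondary analyses comes the sentence "Factors that can affect level of distress will be investigated and adjusted for".
- **Potential covariates:** "Clinical and demographic data included age, length of intimate relationship, education, stage of disease and treatment received for patients", followed by therapeutic alliance and attachment measures. Centre is not listed.

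**The concern.** The design treats centre as important enough to stratify on, and the article gives reasons why distress at five months could differ by centre. The stated primary model does not carry that factor forward.

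Stratified randomisation balances the arms within centres, so the true sampling variance of the treatment effect contains no between-centre component. A regression that leaves centre out still counts that component in its residual. Its standard error is then larger than it need be, its confidence interval wider, and its real type I error below the nominal 5%. What is at stake is some precision on the primary outcome, and some analyst discretion: as written, centre could be added or left out under the open adjustment sentence after the data are seen.

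**Working it through.** **1. The plan's own figures.** The plan gives no figure for centre, so there is none to reproduce on this point. The sample size section sets the scale: SD 16.5, difference 7, alpha 0.05 (taken as two-sided), allocation taken as 1:1. The usual formula, n per arm = 2(z₁₋α/₂ + z₁₋β)² SD²/7², gives 117 per arm (234 couples) at 90% power and 88 per arm (176) at 80%. The article states 220 and 166, which the formula returns exactly with SD 16. That mismatch is a separate matter and does not involve centre. Below I use N = 166, the article's target before its attrition allowance, with the stated SD of 16.5.

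**2. Assumptions.** R is the share of residual IES variance, after baseline adjustment, that is due to centre. The document gives no value; I take 0 to 10%. r is the correlation of baseline with follow-up IES, also not given; I show r = 0 first, then r = 0.6.

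**3. Formulas.**
- SE reported without centre = SD·√(1 − r²)·√(4/N)
- SE with centre = the same × √(1 − R)
- Type I error without centre = 2[1 − Φ(1.96/√(1 − R))]
- Power without centre = Φ(7/SE with centre − 1.96/√(1 − R))
- Power with centre = Φ(7/SE with centre − 1.96)

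The SE with centre also appears in the power without centre because stratification makes it the true sampling SE in either case.

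**4. Results at N = 166, r = 0.** SE without centre = 16.5 × √(4/166) = 2.561.

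| R | √(1 − R) | SE with centre | Type I error without centre | Power without centre | Power with centre |
|---|---|---|---|---|---|
| 0 | 1 | 2.561 | 5.0% | 78.0% | 78.0% |
| 1% | 0.995 | 2.548 | 4.9% | 78.1% | 78.4% |
| 2% | 0.990 | 2.536 | 4.8% | 78.3% | 78.8% |
| 5% | 0.975 | 2.496 | 4.4% | 78.6% | 80.1% |
| 10% | 0.949 | 2.430 | 3.9% | 79.2% | 82.1% |

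The SE falls by 0.5%, 1.0%, 2.5% and 5.1% for R = 1%, 2%, 5% and 10%. Power rises by 0.3 to 2.9 percentage points.

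**5. The same with r = 0.6.** SE without centre = 16.5 × √(1 − 0.36) × √(4/166) = 2.049. At R = 0, power for 7 points is Φ(7/2.049 − 1.96) = 92.7%. At R = 10%, power without centre is Φ(7/1.944 − 1.96/0.949) = Φ(1.535) = 93.8%, and with centre 95.0%. The relative change in SE is as before, but the gain in power is smaller.

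**6. Check by simulation.** Regressions with and without centre were simulated with exact balance within three centres, assumed centre shares of 35%, 40% and 25%, N = 166, r = 0.6 and 6,000 replicates under the null. Mean SE without and with centre was 2.05 and 2.04 (R = 1%), 2.05 and 2.00 (5%), and 2.05 and 1.95 (10%). Type I error without centre was 5.0%, 4.5% and 4.0%, in line with the formula.

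**7. Cost of the extra terms.** Three centres need two parameters. With 166 couples the residual degrees of freedom go from 163 to 161.

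**The case against.** The strongest reply is that this is silence and not error. The article is condensed, the full protocol and SAP are not shown, and the stratification factor may be named there. The methods sentence does not say that baseline is the sole covariate, and "Factors that can affect level of distress will be investigated and adjusted for" could take in centre. The list of potential covariates describes data that had to be collected; centre is known from randomisation and would not need listing. All of this stands against a reader inferring that the plan excludes centre: it does not say so. But the article does not defer the primary model. It gives the model type and the covariate, and a model with centre would differ from that statement. A stratification factor is known in advance and is better fixed than left to an open investigation.

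The case that centre is prognostic can also be pressed too far. The in-house psychologist at Centre 1 is a trial psychologist, and the intervention section bars consulting trial psychologists outside the study until the 10-month follow-up. That largely removes this difference before the primary endpoint. The Centre 3 seminar and its later recruitment period remain. The link between psychologists and centres bears on the intervention arm, so it points to a treatment effect that varies by centre, which a centre main effect does not model. I do not rely on it.

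Two stronger readings are tempting and fail:

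- **That the primary confidence interval and p-value are invalid.** The estimate without centre is unbiased and the test errs, if at all, on the conservative side.
- **That the trial is already short of its stated power, so the loss is serious.** The 78% above ignores the gain from baseline adjustment; at an assumed r = 0.6 power is about 93%. The document does not settle r, so a shortfall is not established.

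**Conclusion.** The point holds as a small improvement in specification. The stated primary model names baseline IES and not centre, although centre was the stratification factor and the article expects centres to differ in usual care. The consequence is at most a modest loss of precision: about 0.5% to 5% of the standard error, and a type I error of 4.9% down to 3.9%, for an assumed centre share of 1% to 10% of residual variance. These figures rest wholly on that assumed share and on 1:1 allocation within centres. If centre does not predict IES change after baseline adjustment, the gain is nil. There is no bias and no inflated error. The case for the change is that it costs almost nothing, matches the analysis to the randomisation, and settles the handling of centre before the results are known.

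**What to change.** In Statistical methods, state that change in IES from T1 to T2 will be analysed by linear regression with treatment, baseline IES and centre (three levels) as fixed effects. Include centre in the same way in the multilevel models for the secondary outcomes. Add that the sentence on adjusting for factors that affect distress applies to secondary or exploratory analyses only, so that the primary model is closed.

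The cost is a few words and two degrees of freedom. Centre is already recorded for every couple, so no new data are needed. The change should be made before outcome data are analysed by arm.

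### Therapeutic alliance, scored only in the intervention arm and only at T2, cannot be a covariate or moderator of the between-arm effect

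*Protocol article*

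**What the plan says.** Four statements in the protocol article bear on this.

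- **Statistical methods, primary outcome.** The change in patients' IES from T1 to T2 "will be analysed with a linear regression, adjusted for baseline". No other covariate is named.
- **Statistical methods, later in the same paragraph.** After the sentences on secondary outcomes and secondary analyses: "Factors that can affect level of distress will be investigated and adjusted for". No factors are listed here.
- **Potential covariates.** The section names age, relationship length, education, disease stage, treatment received, attachment and alliance. On alliance it says "The therapeutic alliance between participants in the intervention group and the psychologists was assessed by participants", using the Bond subscale, "which was only measured at T2".
- **Discussion.** "We have included therapeutic alliance and attachment-related anxiety and avoidance as potential covariates", followed by "Thereby we can ascertain potential moderating effects in the relationship between the participants and the psychologists".

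**The concern.** A covariate or moderator of a randomised comparison must be defined in both arms and must not be affected by allocation. Bond fails on both counts. Control couples had no trial psychologist with whom to form an alliance, so the score does not exist for them. In the intervention arm it is recorded after randomisation, at the same visit as the primary outcome, and it arises from the treatment itself.

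If Bond enters a between-arm model, either no treatment effect can be estimated or the estimate depends on whatever value is invented for the controls. If an association between Bond and distress is reported as moderation of the treatment effect, readers will take it for a randomised finding, which this design cannot supply.

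**Working it through.** The plan gives no figure for this point, so there is none to reproduce. The check is whether the models can be fitted and what they would estimate.

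**Timing.** The Abstract puts randomisation at about 2 months after surgery, delivery within 3 months and T2 at 5 months; 2 + 3 = 5, so T2 falls at about the end of treatment. The section on the intervention also lets couples schedule the first session up to two months after randomisation, at about 2 + 2 = 4 months after surgery. Such couples may still be in sessions at T2. So the exact description of Bond is post-randomisation, not always post-treatment.

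**Model.** Let A = 1 for intervention and 0 for control, X = baseline IES and B = Bond:

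Y = b0 + b1·A + b2·X + b3·B + error

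1. *Complete cases.* B is missing for every control, so all controls drop out. Then A = 1 throughout and its column equals the intercept. The four columns have rank 3, and b1 cannot be estimated.

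2. *Controls coded 0.* The Bond column becomes A·B. Its interaction with arm is A·(A·B) = A·B, because A² = A. The main effect and the interaction are the same column. The five columns (intercept, A, X, Bond, A×Bond) have rank 4, so moderation is not identifiable.

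3. *Controls coded at any constant c.* The Bond column is c·(1 − A) + A·B = c − c·A + A·B, a linear combination of the intercept, A and the interaction. The rank is again 4 of 5. Without the interaction, b1 compares treated couples at Bond = c with controls, so the analyst's choice of c sets the answer.

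**Illustration, under assumptions that are not in the protocol.** N = 166 in equal arms; true effect −7 points; baseline slope 0.6; residual SD 12; Bond mean 20 and SD 4, correlated 0.5 with an unmeasured prognostic factor (SD 1) that lowers IES by 4 points per SD. Bond itself has no effect on the outcome. The within-arm slope of outcome on Bond is then −(4 × 4 × 0.5)/4² = −8/16 = −0.5 point per Bond point. The expected arm coefficient is −7 + 0.5 × (20 − c).

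| Model | Expected b1 | Simulated mean (empirical SE), 4,000 runs |
|---|---|---|
| Baseline only | −7 | −7.0 (2.0) |
| Plus Bond, controls coded 0 | −7 + 10 = +3 | +3.1 (7.3) |
| Plus Bond, controls at treated mean | −7 + 0 = −7 | −7.0 (2.0) |

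Zero coding reverses the sign, because it extrapolates to a Bond score of 0. Mean filling leaves the estimate where it was, so it adjusts for nothing. The slope of −0.5 also arises although Bond does nothing in this model, which is why even the within-arm association should not be read causally.

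**The case against.** The strongest reply is that no model containing Bond is actually written down. The adjustment sentence names no factors, and the covariate list is headed as potential. The Discussion places the moderation in the relationship between participants and psychologists, which exists only in the intervention arm, so a within-arm analysis may be what was meant. The one explicit example there of who might benefit more uses attachment-related anxiety, which is not specific to one arm. These points stand in part: a within-arm analysis is feasible, and T1 attachment scores are proper moderators. But the text does call alliance a covariate, does tie it to moderating effects, and does not confine it to one arm. No analysis plan could make that use valid; it could only withdraw it.

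A reader might also infer that covariates will be picked by their observed relation to distress, so that the primary p-value depends on the model chosen. The document does not support this. It fixes the primary model with baseline adjustment only, the open sentence comes after the secondary-analysis sentences, and no selection rule is stated. Details of covariate selection may properly sit in an analysis plan that is not shown.

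Two further inferences go beyond the text. Treatment received could include treatment given after randomisation, and attachment was apparently measured again at T2 and T3. The document does not say that either later value will be used for adjustment.

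**Conclusion.** The point holds for the further adjusted and moderator analyses. Bond cannot adjust or moderate the between-arm effect. Complete-case use loses 100% of controls, and coding controls at zero or any other constant leaves moderation unidentified. These results follow from where and when Bond is measured and need no assumption about effect sizes. The shift from −7 to +3 is only an illustration under the assumptions listed.

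The stated primary analysis is not shown to be at risk. The link from the adjustment sentence to Bond runs through the Potential covariates section and the Discussion, not through that sentence alone. This is a wording defect that should be corrected before the adjusted and moderator analyses are reported.

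**What to change.** Three changes to the analysis wording:

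- State that the open adjustment sentence does not apply to the primary model, which contains arm and baseline IES, plus centre because randomisation was stratified by centre. Centre is the one addition to the stated model; it rests on the stratification, not on the Bond problem.
- Limit any further adjustment or moderator analysis to a fixed list of variables measured or decided before randomisation, including T1 attachment scores. This also settles which treatment variables and which attachment scores are meant.
- Remove Bond from the covariates and moderators of the treatment effect. Report it only as an association within the intervention arm, labelled non-causal.

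No new data are needed. The cost is that the alliance result becomes descriptive and cannot be presented as showing who benefits from the intervention.
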